## Abstract

**Background:**

The need for structured education programmes for type 2 diabetes is a high priority for many governments around the world. One such national education programme in the United Kingdom is the DESMOND Programme, which has been shown to be robust and effective for patients in general. However, these programmes are not generally targeted to people with intellectual disabilities (ID), and robust evidence on their effects for this population is lacking. We have adapted the DESMOND Programme for people with ID and type 2 diabetes to produce an amended programme known as DESMOND-ID.

This protocol is for a pilot trial to determine whether a large-scale randomised trial is feasible, to test if DESMOND-ID is more effective than usual care in adults with ID for self-management of their type 2 diabetes, in particular as a means to reduce glycated haemoglobin (Hb1Ac), improve psychological wellbeing and quality of life and promote a healthier lifestyle. This protocol describes the rationale, methods, proposed analysis plan and organisational and administrative details.

**Methods/Design:**

This trial is a two arm, individually randomised, pilot trial for adults with ID and type 2 diabetes, and their family and/or paid carers. It compares the DESMOND-ID programme with usual care. Approximately 36 adults with mild to moderate ID will be recruited from three countries in the United Kingdom. Family and/or paid carers may also participate in the study. Participants will be randomly assigned to one of two conditions using a secure computerised system with robust allocation concealment. A range of data will be collected from the adults with ID (biomedical, psychosocial and self-management strategies) and from their carers. Focus groups with all the participants will assess the acceptability of the intervention and the trial.

**Discussion:**

The lack of appropriate structured education programmes and educational materials for this population leads to secondary health conditions and may lead to premature deaths. There are significant benefits to be gained globally, if structured education programmes are adapted and shown to be successful for people with ID and other cognitive impairments.

**Trial registration:**

Registered with International Standard Randomised Controlled Trial (identifier: ISRCTN93185560) on 10 November 2014.

## Background

Type 2 diabetes (T2D) affects approximately one in twenty people across Europe and accounts for an uneven use of healthcare resources [15]. Traditional management of T2D is based on medication, diet and lifestyle modifications, and managed by the patient’s GP, practice nurse and/or diabetes specialist nurse (DNS), with three monthly visits to the health centre [6]. However, many patients find this management strategy difficult to implement and sustain [22]. The need for structured, rather than *ad hoc*, patient education programmes for diabetes using both a theoretical rationale and cognitive reframing has a high priority on the governmental healthcare agenda in the United Kingdom ([10,21]. One specific national programme, the Diabetes and Self-Management for Ongoing and Newly Diagnosed patients with T2D Programme (DESMOND), has been shown to be a robust and effective programme for those with T2D, illustrating improvements in weight loss, depression, smoking cessation, beliefs about diabetes and greater perceived responsibility [5,11,16,23,28].

There is growing evidence to show that as people with ID live longer, they are becoming more susceptible to a range of chronic physical health conditions, such as respiratory disease, cardiovascular disease, gastrointestinal and gall bladder cancers, and T2D [30,38]. Although limited information exists on the incidence of diabetes in people with ID, McVilly *et al*. [20] in a systematic review reported that people with ID are more likely to develop T2D compared to their non-ID peers: approximately 8% (range: 3% to 18%) rather than 4% in the non-disabled population [15]. This increased risk may result from the ID population being more likely to have poor nutrition, consume high fat foods, undertake less physical activity and lead more sedentary lifestyles, resulting in greater levels of obesity [13,34,38]). Lennox *et al*. [17] in Australia, Shireman *et al*. [26] in Canada and [name] *et al*. [32] in Northern Ireland found that a considerable proportion of people with ID living in the community also had T2D, which was poorly managed. Further, people with ID have had few opportunities to engage in diabetes health education and screening [26,32,33].

Internationally, reports have highlighted the continued neglect of the health of people with ID, and that healthcare services consistently fail to work together and make reasonable adjustments to meet the health needs of this population [7]. With a national focus on health disparities and health promotion in the non-disabled population, it is important that health issues that have not been addressed are identified and acted upon for all vulnerable populations; further illustrating the ongoing health inequalities this population face [9].

The robust structured education programmes developed to improve the biomedical, psychosocial and self-management strategies for non-disabled people with type 1 and 2 diabetes have not been targeted to adults with ID [32,]. For example, [name], Brown & Karatzais (2014) [33] reported that there was a lack of appropriate information on diabetes and diet management for people with ID, and that little emotional support was being offered to adults with T2D who had ID. People with ID rarely accessed structured education programmes for diabetes that were offered to the non-disabled population [29]; further illustrating ongoing inequality and disadvantage [8]. These programmes have neither recognised nor addressed the specific challenges posed by this population’s cognitive deficits, communication difficulties, low levels of literacy skills and different learning styles. There is also a lack of adequate attention to the need to support family and paid carers [13].

A search for other research found no trials pertaining to diabetes education for people with ID in the World Health Organization’s International Clinical Trials Registry Platform [24]. Likewise, we have not identified any structured education programmes being delivered internationally that are specifically tailored to the needs of adults with ID and T2D, or that target the carers who support this population. In view of the burden and severity of diabetes, it is essential that adults with ID and their family and/or paid carers are afforded the opportunity of an evidence-informed education programme that meets the National Institute of Clinical Excellence Standards [21].

### Study objectives

With funding from Diabetes UK, [name] and colleagues have adapted the DESMOND Programme so that it could be used for adults with ID in the United Kingdom. They developed DESMOND-ID through robust delivery and evaluation of the original DESMOND education programme over 18 months, using video-recordings, focus groups with service users and their carers, feedback from two DESMOND Programme educators and observations from three independent health professionals.

The key research question is: Can we design a feasible, large-scale randomised trial that will resolve uncertainty and determine whether DESMOND-ID is more effective than usual routine care in helping adults with ID to better self-manage their T2D to reduce their Hb1Ac? In order to answer this question, we will conduct a small pilot randomised trial comparing the use of the DESMOND-ID programme with usual routine care across three countries in the United Kingdom (Northern Ireland, Scotland and Wales). This pilot trial will include carefully selected secondary outcome measures (body mass index (BMI) waist circumference, blood pressure, lipid profiles, cardiovascular disease (CVD) risk score, smoking, alcohol use, exercise, perceptions and severity of beliefs, and quality of life), in addition to the primary outcome measure of Hb1Ac.

People with ID have had very few opportunities to participate in randomised trials about their healthcare, and no dedicated guidance has been published on undertaking a pilot randomised trial with this population. Therefore, our development of this protocol used general recommendations for clinical trial protocols proposed by Tetzlaff *et al*. [35] and the Consolidated Standards of Reporting Trials (CONSORT) 2010 guidelines [25]. This pilot randomised trial will enable us to:Examine the feasibility of delivering the DESMOND-ID programme.Assess eligibility, consenting rate, attendance levels, recruitment process, loss to follow-up, compliance and Hb1Ac of adults with ID and T2D.Determine the acceptability of randomisation to adults with ID and their carers, using retention rates as a surrogate for acceptability [3].Determine the appropriateness and the acceptability of the outcome measures to adults with ID through completion rates, in order to see whether the primary outcome measure (HbA1c) and secondary outcome measures (BMI, waist circumference, blood pressure, lipid profiles, CVD risk score, smoking, alcohol use, exercise, perceptions and severity of beliefs, and quality of life) can be collected.Determine the appropriateness and acceptability of the outcome measures for the family and paid carers through completion rates.Measure compliance of the educators in delivering the DESMOND-ID programme.Estimate the treatment effect to determine whether this suggests a clinically important effect which will support the conduct of the full trial.

We will also conduct focus groups with adults with ID, their carers and educators to assess the acceptability of the intervention and the trial, and to explore their experience of the education programme, including any barriers and/or facilitators to adherence.

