#### Psychosocial or behaviour measures

Participants with ID will complete the following measures at baseline and at three months after the intervention:The Illness Perception Questionnaire-Revised [39] will examine participants’ understanding of diabetes (illness coherence score), perception of the duration of their illness (timeline score) and the perception of their ability to affect the course of their diabetes (personal responsibility score). This scale has not been validated for adults with ID.The Diabetes Illness Representation Questionnaire [27] will examine participants’ perceptions about the seriousness and impact of diabetes. This scale has not been validated for adults with ID.The Summary of Diabetes Self-Care Activities Questionnaire [36] will examine participants’ diet and smoking patterns. This scale has not been validated for adults with ID.The International Physical Activity Questionnaire [4] will examine participants’ physical activity. This scale has been validated for adults with ID.

The research team may need to support the person with ID by reading the instructions and items aloud. As part of the revision of the original DESMOND Programme, [name], [name], [name], [name], [name], [name], *et al*. unpublished work) amended these standardised questionnaires in terms of wording, layout and employing a more user friendly Likert response for the items (using smiling faces instead of a numerical scale). The scales psychometric properties will be tested to examine if these instruments are stable for this population. The statistician will be blinded as to which participants are in the intervention and control groups.

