### Follow-up

Follow-up assessments of all biomedical and psychosocial measurements will be undertaken three months directly after the intervention has been delivered, with adults with ID and their carers, for both groups across the three countries. The biomedical measurements will be collected by either the DNS or practice nurse, and the psychosocial measurements will be collected by the research associates.

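### For the questionnaires, completion rates show that forms can be collected; they are a weak test of whether the measures are appropriate for adults with ID

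*Protocol article*

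**What the plan says.** Under Study objectives, the article will "Determine the appropriateness and the acceptability of the outcome measures to adults with ID through completion rates". The sentence then gives its purpose, "in order to see whether the primary outcome measure (HbA1c) and secondary outcome measures" can be collected, and its list runs from BMI and blood pressure to illness beliefs and quality of life. One criterion therefore covers laboratory values, physical measurements and self-report alike.

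Psychosocial or behaviour measures names four questionnaires. For three of them (Illness Perception Questionnaire-Revised, Diabetes Illness Representation Questionnaire, Summary of Diabetes Self-Care Activities) it states: "This scale has not been validated for adults with ID". For the International Physical Activity Questionnaire it states: "This scale has been validated for adults with ID". The instruments were amended in wording and layout and by "employing a more user friendly Likert response for the items (using smiling faces instead of a numerical scale"; the physical activity scale is not exempted from these changes. On administration: "The research team may need to support the person with ID by reading the instructions and items aloud". On measurement quality: "The scales psychometric properties will be tested to examine if these instruments are stable for this population".

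Under Follow-up, "the psychosocial measurements will be collected by the research associates". Under Focus groups, the participants invited are those who received the intervention, and acceptability of every element of the trial is among the topics.

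**The concern.** A blood result that is present is nearly always usable. A questionnaire that is present may not be. The Background describes this population as having cognitive deficits, communication difficulties and low literacy. With an amended, mostly unvalidated scale and a helper available, a form can be filled in by agreeing with each item or choosing the same face throughout. The completion rate counts that form as a success.

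The pilot exists to design a full trial, and the article intends to compare effects with those in people without ID (Measures for participants with intellectual disabilities). Both uses need scores that mean something. If high completion alone settles appropriateness, a scale with poor response quality could go forward unnoticed.

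A second, smaller issue is that help is not described as standardised or recorded. If it varied by arm or visit, scores could differ for reasons unrelated to the programme.

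**Working it through.** **Inputs from the article.** N = 36, which reproduces as 18 + 18 and as 12 × 3 countries. There are four questionnaires and two visits (baseline and three months after the intervention). No expected or target completion rate is stated. All completion probabilities and correlations below are assumptions.

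**Scale.** Before any loss to follow-up there are 36 × 4 × 2 = 288 participant forms, of which 36 × 3 × 2 = 216 are on scales stated to be unvalidated in ID.

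**Step 1: what a high completion rate shows.** Let p be the probability that a form is completed, regardless of understanding. For one scale at one visit,

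P(at least 35 of 36 complete) = p^36 + 36 × p^35 × (1 − p).

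| assumed p | P(at least 35 of 36) |
|---|---|
| 0.95 | 0.46 |
| 0.98 | 0.84 |
| 0.99 | 0.95 |

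Understanding does not enter the formula. If 36 of 36 forms were complete, the exact 95% interval would be 90.3% to 100%. That is a precise statement about collection and says nothing about meaning.

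**Step 2: whether the stability testing would catch it.** Take a scale of k items scored in one direction. Suppose each person picks one face for every item at both visits, and different people favour different faces (variance s² between people). The item variances sum to k·s², and the total score has variance k²·s².

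- Cronbach's alpha = k/(k − 1) × (1 − k·s²/(k²·s²)) = k/(k − 1) × (1 − 1/k) = 1.
- Each person's total is the same at both visits, so the retest correlation is also 1.

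This is an extreme case chosen to show direction. Reverse-scored items would lower alpha, but the retest correlation stays at 1 as long as totals still vary between people. The article does not say which psychometric statistics will be used.

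**Step 3: how much the stability testing can say.** The only two questionnaire visits lie either side of the intervention, so only the 18 controls give a retest free of it. With Fisher's z, the limits are tanh(atanh(r) ± 1.96/√(n − 3)). For an assumed r = 0.7:

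- n = 18: 0.35 to 0.88
- n = 36: 0.48 to 0.84

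**Step 4: the other checks.** The abstract describes focus groups with all participants, whereas the Focus groups section limits the participant groups to those who received the intervention; the two should be reconciled. Either way, acceptability is not response quality. The only recall check described is under Ethical considerations, and it concerns consent.

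**Step 5: help and allocation.** Under Randomisation, the research team is told each allocation. Research associates collect the psychosocial follow-up. Blinding is stated only for the statistician. Differential help is therefore possible, but the article neither says the associates know the allocation nor that help differs.

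**The case against.** The strongest reply is that the sentence is about collectability: its own purpose clause says so, it covers clinical measures for which completion is the natural test, and this is a feasibility pilot. Completion is also not the only check, since psychometric testing and focus groups are planned. Both arms have the same assessments, so intervention participants can comment on the same forms. Scripts and tick-boxes usually belong in the full protocol or case report form, and the adaptation work is described in a manuscript not shown here.

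Much of this stands. A reader might infer that completion is the sole safeguard, that staff routinely read every item, or that scales nobody understands will pass at near 100%. The documents support none of these: psychometric testing is planned, reading aloud is conditional, and no completion or comprehension figure is given. A reader might also treat unaided completion as a measure of understanding. It is not one. Reading aloud is a reasonable adjustment for low literacy; a person may understand a spoken item, and an unaided form can be ticked without thought.

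What does not fall away is the criterion itself. The article fixes it, names appropriateness as well as acceptability, and does not connect it to the psychometric testing. Neither that testing nor the focus groups is directed at uniform or acquiescent answering.

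**Conclusion.** The point holds in a limited form. Completion is sound for the clinical measures and for collectability generally. For the questionnaires, especially the three unvalidated ones, it is insufficient evidence of appropriateness, and the planned stability testing neither feeds into the stated objective nor reliably detects patterned responding.

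The size cannot be estimated from the documents. The probabilities of 46% to 95% rest on assumed completion rates of 0.95 to 0.99, and the correlation limits on an assumed r of 0.7. They show what completion and retest figures can and cannot establish at this sample size, not what will happen in this trial. Differential help by arm is a risk to monitor, not an established bias. This is an inexpensive improvement to a stated criterion, worth making before the pilot's results are used to choose outcomes for the full trial.

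**What to change.** 1. Keep completion rates as the test of whether every measure can be collected.
2. For the questionnaires, reword the objective so that appropriateness is judged on four things together: completion, the psychometric results already planned, item-level missingness, and the share of forms with one identical response throughout.
3. For each scale and visit, record the level of help (none / read aloud / explained / carer answered). Report it by arm and visit as a descriptor and a possible source of differential measurement, not as a measure of comprehension.
4. Use the same read-aloud script in both arms.

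Item missingness and identical-response shares come from data already being collected. The added work is one tick-box per form (at most 288) and a short descriptive table. If the full protocol or the adaptation manuscript already contains these elements, a cross-reference in the objective is enough.

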## Methods/Design

The study is a two arm, individually randomised, pilot trial in adults with ID and T2D, and their family and/or paid carers. It compares the DESMOND-ID programme with usual routine care. Figure 1 illustrates the pathway through the trial. This trial corresponds to phase 2 of the Medical Research Council’s [18,19] guidelines for complex interventions: assessing feasibility.

**Figure 1 Fig1:**
[figure not shown]
Flowchart of the study protocol. ID (intellectual disabilities).

### Recruitment

#### Participants

ID is defined by significant limitations in both intellectual functioning and adaptive behaviour, which cover many everyday social and practical skills, and it originates before the age of 18 years [1]. Adults with mild to moderate ID with T2D from three countries in the United Kingdom (Northern Ireland, Scotland and Wales) will be recruited. A sample of 36 individuals in total will be included in this pilot study: 18 people with ID in the intervention group and the same number in the control group (N = 18). There will be 12 participants from each country; the participants will all come from one area per country. Where there are family and/or paid carers, they will also be recruited, and participants with ID who do not have a carer will also be included.

#### Recruitment strategy

In a study that examined the demographics, health and diabetes quality-of-care indicators of 186 people with ID in Northern Ireland, [name] *et al*. [32] highlighted the difficulties in identifying and recruiting this population.

Therefore, potential participants will be recruited from ID statutory services and can also be self-referred or referred by their GP, practice nurse, DSN or community ID nurse, or by the family or paid carer in response to posters and flyers about the project. These will be placed in ID day centres, health centres and so forth.

#### Inclusion criteria

The eligibility criteria will require that participants must be 18 years of age or older, living in the community, with mild to moderate ID and T2D, identified in their clinical notes by the ID team, GP, practice nurse or DSN. The definition of a family or paid carer is someone who is either a family relative or residential member of staff who engages in the support of the person with ID. Verbal and/or written consent will be required from people with ID and from their carers before they enter the study.

#### Exclusion criteria

Participants with any one of the following criteria will not be eligible: type 1 diabetes, a severe or profound ID as assessed by the community ID team, inability to communicate and inability to give their verbal and/or written consent.

#### Consent

Participants with ID will be screened for eligibility by the primary healthcare team or community ID nurse, who will provide the potential participants with a user friendly information sheet and consent form. Participants with a family and/or paid carer will also be provided with an information sheet and consent form. It is only after consent has been obtained that the research team will contact the participant and their carer to arrange baseline data collection.

